### Outcomes

The primary endpoint is the percentage of patients receiving an out-of-hours, face-to-face consultation with a GP, or who are admitted to hospital, during the 2 weeks following their call to the centre. The motive for the consultation or hospital admission should be the same as the motive initially prompting the call. Secondary endpoints are the following variables measured over the 2 weeks: number of stays in intensive care, number of hospital admissions, number of interventions by the fire brigade, emergency medical and ambulance services, number and length of prescribed sick leave episodes, all-cause mortality, morbidity, clinical outcome, patient compliance, patient satisfaction, number of renewed calls to the call centre, number of patients receiving multiple face-to-face consultations and costs incurred.

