**Methods/design:**

This is a prospective, open-label, multicentre, pragmatic, cluster randomised clinical trial of an estimated 2880 patients making an out-of-hours call to one of six French emergency call centres for assistance with either fever or symptoms of gastroenteritis without seriousness criteria. Each call is handled by a call centre physician. Out-of-hours is 8 p.m. to 7.59 a.m. on weekdays, 1 p.m. to 7.59 a.m. on Saturdays and round-the-clock on Sundays and school holidays. Patients will be enrolled over 1 year.

In the intervention arm, a telephone consultation based on a protocol, the formal Telephone Medical Advice (fTMA), is offered to each patient calling. This protocol aims to overcome a physical consultation during out-of-hours periods. It offers reassurance and explanations, advice on therapeutic management which may include, in addition to hygiene and diet measures, a telephone prescription of antipyretic, analgesic, rehydration medication or others, and recommendations on surveillance of the patient and any action to be taken. The patient is invited to call again if the condition worsens or new symptoms develop and to make an appointment with their family GP during office hours. In the control arm, the call centre physician handles calls as usual. This physician can carry out a telephone consultation with or without a telephone prescription, dispatch an on-duty GP, the fire brigade or an ambulance to the patient, or refer the patient to an on-duty physician or to the ED. Each patient will receive a follow-up call on day 15.

The primary endpoint is the frequency of out-of-hours, face-to-face GP consultations or visits to the ED during the 15 days following the index call. The secondary endpoints measured on day 15 are the number of stays in intensive care, the number of hospital admissions, the number of interventions by the fire brigade, emergency medical and ambulance services, the number and length of prescribed sick-leave episodes, all-cause mortality, morbidity, clinical outcome, patient compliance, patient satisfaction, the number of renewed calls to the call centre, the number of patients receiving multiple face-to-face GP consultations and costs incurred.

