### Economic evaluation

Only health care (acute) resources are considered. Intervention costs are obtained with a bottom-up microcosting approach that identifies all relevant cost components of the telephone intervention and values each of those components for all individual patients using the following variables: duration, staff, and equipment. Consultations, sick leave, drugs and other resources and emergency interventions for each patient are recorded in the electronic Case Report Form (eCRF) or retrieved from the hospital databases. The prices of drugs, consultations and an emergency ambulance are based on national tariffs. Hospitalisation costs are estimated from the average national cost of each patient’s diagnosis-related groups weighted with their actual length of stay and resources used during their hospitalisation (intensive care, blood transfusion, etc.). The time horizon is 15 days.

For the purpose of the cost-effectiveness analysis, we define a composite endpoint of adverse events combining hospital admissions, emergency visits and 15-day mortality. A cost-effectiveness analysis is conducted to assess incremental cost per adverse event averted. The cost-effectiveness analysis focusses on estimation of the joint density of cost and effect differences and quantification of uncertainty surrounding the incremental cost-effectiveness ratio. The absence of a significant difference in either cost or effectiveness, or both, does not preclude the presentation of such data on the cost-effectiveness plane [15, 16].

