### Sample size

We postulate that fTMA will reduce the percentage of out-of-hours on-duty GP consultations or the number of visits to an ED during the 2 weeks following the index call. In the study by Lattimer et al., the percentage of hospital admissions and ED visits was 12 % after a nurse telephone consultation [17]. In a parallel study, Thompson et al. reported a 21 % versus a 33 % overnight call rate resulting in a home visit by a duty GP in the nurse telephone intervention arm versus the control arm [18]. We estimate that the percentage of out-of-hours consultations and ED visits (our primary endpoint) will be 50 % in the control group. We aim for an absolute reduction of at least 10 % (i.e. from 50 to 40 %) in the intervention arm for each indication (fever/gastroenteritis).

On the assumption of a relatively low weak design effect due to cluster randomisation (about 1.5), and considering a loss of follow-up of 15 %, it is estimated that a sample size of 663 patients/arm/indication will be required for 85 % power and a 5 % alpha risk. If account is taken of an attrition rate of about 8 %, 720 patients will be required (1440/indication, i.e. a total of 2880 patients). This sample size should provide enough power and precision for subgroup analyses (season versus diurnal cycle, weekend versus weekdays).

Inclusions will take place over a full year in order to obtain a representative sample. Each centre will thus include about 240 patients for each indication. A random sample of four patients per week will be drawn outside of an epidemic (about 42 weeks) and of eight patients per week during an epidemic (about 10 weeks) in each centre for each indication. For feasibility reasons, the first patient whose call is closest to the dates and times that will have been randomly drawn for each week of the year of study will be included for each indication.

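### The primary endpoint has two incompatible definitions: Outcomes counts hospital admission, while the abstract and the sample size count ED visits

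*Protocol article*

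**What the plan says.** The protocol article defines the primary endpoint in three places.

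- Outcomes: "The primary endpoint is the percentage of patients receiving an out-of-hours, face-to-face consultation with a GP, or who are admitted to hospital", over two weeks. It adds: "The motive for the consultation or hospital admission should be the same as the motive initially prompting the call".
- Abstract, Methods/design: "The primary endpoint is the frequency of out-of-hours, face-to-face GP consultations or visits to the ED during the 15 days following the index call". No condition on motive is given.
- Sample size: "We estimate that the percentage of out-of-hours consultations and ED visits (our primary endpoint) will be" 50% in the control group, with a target of 40% in the intervention arm for each indication. Again there is no condition on motive, and the window is two weeks.

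Two further places bear on whether admission and ED visit could mean the same thing. The secondary endpoints in Outcomes include "number of stays in intensive care, number of hospital admissions". The Economic evaluation section builds a "composite endpoint of adverse events combining hospital admissions, emergency visits and 15-day mortality".

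**The concern.** The three statements do not describe one variable. Under the abstract and Sample size, a visit to the ED that ends in discharge is an event. Under Outcomes it is not, unless the patient also had an out-of-hours face-to-face GP consultation. In the other direction, an admission that bypasses the ED is an event under Outcomes only. The abstract also speaks of a frequency over 15 days, where Outcomes speaks of a percentage of patients over two weeks.

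Two things are at stake. First, the power statement is made for one definition and may not hold for the other. Second, with two published definitions and an extra motive condition attached to one of them, the choice could be made after the results are seen. If the Outcomes wording were followed, ED visits without admission would enter no listed primary or secondary contact endpoint. The nearest secondary item is interventions by the fire brigade, emergency medical and ambulance services. Such visits would appear only in the cost-effectiveness composite, although the article says that the intervention is expected to reduce ED visits.

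**Working it through.** **1. Are admission and ED visit used as synonyms?** No. Outcomes lists hospital admissions as a secondary endpoint in its own right, and Economic evaluation names admissions and emergency visits as two components of one composite. The difference is one of content.

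**2. Which definition does the sample size belong to?** Inputs from Sample size: 50% versus 40%, 85% power, design effect 1.5, attrition 8%. From Statistical analyses: two-sided 5% alpha. With pooled variance under the null and no continuity correction,

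n = [1.960 × √(2 × 0.45 × 0.55) + 1.036 × √(0.50 × 0.50 + 0.40 × 0.60)]² / 0.10² ≈ 443 per arm.

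- Design effect: 443 × 1.5 = 664.5, against 663 stated (442 × 1.5 = 663 exactly).
- Attrition: 663 / 0.92 = 720.7, against 720 stated.
- Power with 663 evaluable per arm (663 / 1.5 = 442 effective): 84.9%, against 85% stated.

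The plan's figures reproduce, and they rest on rates that the article attaches to consultations and ED visits. (They reproduce without the 15% loss to follow-up that the same sentence mentions. That is a separate matter.)

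**3. What would the same sample give for the admission version?** The document has no rate for it, so the control rates below are assumptions. Power is for 720 × 0.92 / 1.5 = 441.6 effective patients per arm. Required N is evaluable patients per arm per indication, including the design effect.

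| Assumed control rate | Required N, 10-point reduction | Power | Required N, 20% relative reduction | Power |
|---|---|---|---|---|
| 50% | 665 | 85% | 665 | 85% |
| 40% | 611 | 88% | 968 | 70% |
| 30% | 504 | 93% | 1473 | 52% |
| 20% | 342 | 99% | 2483 | 34% |

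Power may rise or fall, depending on whether the effect is constant on the absolute or the relative scale. The table shows only that the stated 85% cannot be carried over to the admission version.

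**4. Can the direction of any bias be found?** Let d_C and d_I be the shares of control and intervention patients whose only qualifying contact is an ED visit without admission. Leaving aside admissions that bypass the ED, the between-arm difference under Outcomes equals the difference under the ED version minus (d_C − d_I). The article gives neither share. If d_C exceeds d_I, the Outcomes wording shrinks the apparent benefit. If d_I exceeds d_C, it enlarges it.

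**5. The motive restriction.** Suppose that the true contact rate is 50% in both arms (assumed). If the restriction removes 5% of contacts in each arm, both rates become 50 × 0.95 = 47.5% and no difference arises. If it removes none in control and 10% in the intervention arm, the rates are 50% and 45%, a false difference of 5 points. The document does not indicate whether removal would differ by arm.

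**The case against.** The strongest reply is that this is condensed wording in a journal article. An abstract and a sample-size paragraph need not repeat every condition, and the full protocol may carry one clean definition. That is fair for the motive restriction, whose absence elsewhere may be ordinary shortening. It does not cover admission versus ED visit: these are different events, and Sample size explicitly labels the ED version as the primary endpoint.

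Several stronger readings are tempting, but the document does not support them.

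- A reader might infer that the Outcomes wording favours the intervention, because an advised patient who goes to the ED and is discharged is not counted. The Intervention section lets control-arm physicians refer patients to the ED, and those sent home would go uncounted too. If such visits are commoner under usual care, the wording works against the intervention.
- A reader might take the 12% cited in Sample size, assume that 10 to 30% of ED visitors are admitted, and conclude that 12 − 3.6 = 8.4 to 12 − 1.2 = 10.8 points are lost, as much as the 10-point target. The 12% already combines admissions with ED visits, and the admission share is invented. Patients who also saw an out-of-hours GP still count. The result is also a change of level in one arm, not a difference between arms.
- A reader might infer that the motive restriction hides missed diagnoses. Motive is not diagnosis: a febrile patient who returns with fever and proves to have another illness has the same motive and is counted. Only contacts for a new complaint might drop out. Admissions, intensive care stays and all-cause mortality carry no stated motive restriction.
- A reader might assume that Outcomes governs the analysis, or that motive is judged from the caller's report. The article says neither.

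**Conclusion.** The contradiction stands and concerns the primary endpoint. Outcomes counts a GP consultation or hospital admission; the abstract and Sample size count a GP consultation or ED visit. The 50% and 40% rates, and the 663 and 720 patients per arm per indication, are stated for the ED version only. For the admission version the article gives no rate and hence supports no power figure. The range in the table, 34% to 99%, rests entirely on assumed control rates of 20 to 50% and on the choice of effect scale. The same-motive restriction is stated in one of the three places. Neither the direction nor the size of a resulting bias can be determined from the document, and none is claimed here.

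**What to change.** Before outcome analysis:

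1. Change Outcomes to the endpoint that the sample size uses: the percentage of patients with at least one out-of-hours face-to-face GP consultation or at least one ED visit, admitted or not, within 15 days of the index call.
2. Use the same wording in the abstract, Outcomes and Sample size, including percentage of patients rather than frequency and one window rather than both 15 days and two weeks.
3. Keep hospital admission as the secondary endpoint it already is.
4. State the same-motive restriction consistently wherever the endpoint is defined. Say whether motive means the medical indication or the caller's reason for calling, since Data collection records both. Add an any-motive version of the composite as a sensitivity analysis.

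Removing the motive restriction from the primary endpoint outright is not recommended on this evidence. Inclusion had already ended in July 2016 in an open-label trial, so that would be a change of substance.

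The cost is a text correction and a little extra analysis. Emergency visits are already needed for the cost-effectiveness composite, and the follow-up call is to collect the data for the economic evaluation. The sample size needs no change on this account, because its rates already belong to the ED version.

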## Background

Medical advice provided over the telephone is increasingly common in general practice [1–3]. Most calls made to medical call centres concern issues relating to general practice, in particular out-of-hours care. A widespread response to such calls is a telephone consultation [1]. The advice given may relate to action to be taken in the home including surveillance, and may involve telephone prescription and may invite the caller to consult a general practitioner (GP) [4].

Few prospective studies have addressed the effectiveness of advice given over the telephone in primary care in terms of patient compliance, satisfaction and benefit. Moreover, the impact of telephone advice on health costs has not been properly evaluated. A Cochrane review, which identified only five comparative randomised studies on the possibly superior efficacy of telephone consultations over usual care, concluded that such advice had little impact in terms of fewer visits to the family physician or to the hospital emergency department (ED) [1]. The review recommended that high-evidence level studies be conducted with patient satisfaction, safety and cost as endpoints.

In a study in the UK, in which out-of-hours calls to a general practice cooperative were randomised into two groups – namely, telephone consultations with a nurse versus usual general practice care – there was a reduction in costs arising from reduced emergency admissions to hospital in the nurse consultation group [5]. In a study in two urban practices in Scotland, supported by a UK study, telephone consultations for same-day appointments saved general practitioner (GP) time but led to a higher rate of reconsultations in the 2 weeks that followed [6, 7]. On the other hand, the introduction of telephone triage in another UK study significantly reduced by 39 % the demand for face-to-face consultations for patients seeking same-day appointments [8]. The number of ED visits does not seem to be related to telephone consultations [6–9]. The impact on cost seems negligible [7]. In a recent randomised controlled trial conducted in the UK, telephone triage by a nurse or a GP increased the primary care contact compared with usual care for patients calling for a same-day appointment [10, 11]. However, this trial did not focus on out-of-hours periods.

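### ED visits and out-of-hours GP consultations are not listed as separate endpoints, and the primary endpoint that should combine them is defined in two ways

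*Protocol article*

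**What the plan says.** The primary endpoint appears in three places.

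- Abstract, Methods/design: "frequency of out-of-hours, face-to-face GP consultations or visits to the ED during the 15 days following the index call".
- Sample size: "the percentage of out-of-hours consultations and ED visits (our primary endpoint", assumed to be 50 % in the control arm, with a target of 40 % in the intervention arm for each indication.
- Outcomes: "percentage of patients receiving an out-of-hours, face-to-face consultation with a GP, or who are admitted to hospital", over two weeks and for the same motive as the call.

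The Outcomes section then lists the secondary endpoints: "Secondary endpoints are the following variables measured over the 2 weeks: number of stays in intensive care, number of hospital admissions". The list continues with fire brigade, emergency medical and ambulance interventions, sick leave, mortality, morbidity, clinical outcome, compliance, satisfaction, renewed calls, patients with multiple face-to-face consultations, and costs. The Abstract gives essentially the same list.

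ED visits also appear in the Economic evaluation, in "a composite endpoint of adverse events combining hospital admissions, emergency visits and 15-day mortality". The end of the Intervention section adds that patients whom the call centre physician refers to a duty GP or the ED, or for whom someone is called out, will be identified and analysed.

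**The concern.** The Abstract's Background names out-of-hours GP workload and ED visits as separate matters on which evidence is scant. The intervention acts most directly on the first, because it aims to replace a physical out-of-hours consultation. A caller who is not sent a duty GP may still go to the ED unprompted, so the two components need not move together.

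Under the Abstract and Sample size definition, a fall in GP contacts can offset a rise in ED visits inside the primary endpoint. Under the Outcomes definition, an ED visit without admission is not counted in the primary endpoint at all. In both cases the trial could report a favourable primary result, and no listed endpoint would show separately what happened to ED visits. A reader could then take the result as evidence of fewer ED visits when it is not.

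**Working it through.** **1. Is each component listed on its own?**

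| Component | Abstract / Sample size definition | Outcomes definition | Separate secondary endpoint? |
|---|---|---|---|
| Out-of-hours face-to-face GP consultation | in primary | in primary | no |
| ED visit | in primary | not in primary | no |
| Hospital admission | not in primary | in primary | yes |

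The neighbouring secondary endpoints do not fill the gap. Admissions miss ED visits that end in discharge. Ambulance and fire brigade interventions miss patients who travel by themselves. Multiple consultations miss a single one.

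**2. The plan's own figure.** Inputs (Sample size; Statistical analyses): 50 % v 40 %, 85 % power, two-sided 5 %, design effect 1.5.

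n = [1.96·√(2·0.45·0.55) + 1.036·√(0.50·0.50 + 0.40·0.60)]² / 0.10² = 443 per arm; 443 × 1.5 = 664.5, against the stated 663. Then 663/0.92 = 721, against 720. This match leaves out the 15 % loss to follow-up that the section also mentions (664.5/0.85 = 782), which is a separate matter. Below, 663 is taken as the number analysed, so the effective n is 663/1.5 = 442 per arm per indication.

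**3. Can the components move in opposite directions within the planned result?** Assumptions, not given in the document: no patient has both events, and the control 50 % splits into 38 % GP and 12 % ED. The 12 % is borrowed from the cited nurse telephone study, where it covers admissions and ED visits together in the telephone arm.

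- GP: 38 % to 24 %; ED: 12 % to 16 %; sum: 50 % to 40 %.
- Composite: z = 0.10/√[(0.25 + 0.24)/442] = 0.10/0.0333 = 3.00; power about 85 %.
- GP: z = 0.14/√[(0.2356 + 0.1824)/442] = 0.14/0.0308 = 4.55.
- ED: z = −0.04/√[(0.1056 + 0.1344)/442] = −0.04/0.0233 = −1.72.

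The planned result is met in full while ED visits rise by one third (4/12).

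**4. What would a separate ED comparison show?** With rate p in both arms, the standard error is √[2p(1 − p)/442]. With six randomised centres, a t reference on 6 − 2 = 4 df (2.776) is more realistic than 1.96.

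| Assumed ED rate | SE (points) | ± with 1.96 | ± with 2.776 |
|---|---|---|---|
| 5 % | 1.47 | 2.9 | 4.1 |
| 12 % | 2.19 | 4.3 | 6.1 |
| 20 % | 2.69 | 5.3 | 7.5 |

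With both indications together at 12 %: about 221 patients per centre per indication and a design effect of 1.5 imply an intracluster correlation of 0.5/220. Doubling the cluster size gives 1 + 441 × 0.5/220 = 2.0. The effective n is 1326/2.0 = 663, and the half-width is ±3.5 points (normal) or ±5.0 points (t on 4 df).

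If the 15 % loss has to come out of the 663, the effective n is 663 × 0.85/1.5 = 376, and the per-indication figures at 12 % become ±4.6 and ±6.6 points.

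**The case against.** **Hospital admission is listed.** A reader might infer that neither half of the primary endpoint is an endpoint on its own. Under the Outcomes definition that is wrong, because admission is the second half and is a listed secondary endpoint. What remains under every definition is the absence of separate endpoints for ED visits and for out-of-hours GP consultations.

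**A rise would leave traces.** A reader might also infer that a rise in ED visits would be hidden. The documents do not support that. The economic composite includes emergency visits and excludes GP consultations, so a fall in GP contacts cannot offset a rise there. Referred patients are to be analysed, and hospital and ambulatory costs are considered separately. This objection stands as far as it goes. However, in the composite ED visits are diluted by admissions and deaths, and the referral analysis does not cover patients who go to the ED unprompted.

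**The cited evidence does not predict a rise.** The Background says "The number of ED visits does not seem to be related to telephone consultations", which points to no change. Nor does the document derive its 10-point target from GP home visits: the 21 % versus 33 % figures ("overnight call rate resulting in a home visit by a duty GP in the nurse telephone intervention arm" versus control) are cited, but the 50 % is an estimate and the 10 points an aim. Both objections stand. The concern is that opposite movement is possible, not that it is expected.

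**Component tables may be in the analysis plan.** That plan is not shown, and tabulation can be left to it. But this document sets out an explicit endpoint list and states the primary endpoint inconsistently. Both can be judged here.

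**Conclusion.** The point holds in a limited form. The primary endpoint is defined inconsistently, and under either version the explicit secondary lists omit ED visits and out-of-hours GP consultations as separate endpoints. A favourable primary result would therefore not, on its own, answer the ED question that the Abstract raises.

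The size is illustrative. A 4-point ED rise inside the planned 50 % to 40 % result rests on an assumed 38/12 split, no overlap, and a borrowed 12 %. It shows that the arithmetic allows masking, not that masking is likely.

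A reader might infer that a separate ED endpoint would prove such harm. It cannot be relied on to do so. The illustrated rise (z = −1.72) lies inside the ±4.3-point interval and well inside the ±6.1 points obtained with t on 4 df. The component results would be descriptive: they would guide how the composite is read and rule out only larger rises.

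**What to change.** 1. Reconcile the primary endpoint in Outcomes with the Abstract and Sample size section, so that one definition states whether ED visits, hospital admissions or both count.
2. Add two secondary endpoints to Outcomes: patients with an out-of-hours face-to-face GP consultation, and patients with an ED visit, over the same follow-up period.
3. Report each per indication, beside the primary result, as an arm difference with a cluster-adjusted confidence interval that uses a small-sample correction for six centres.
4. State that no reduction in ED visits will be claimed from the composite alone.

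The cost is a corrected definition, one further sentence and two table rows. The sample size does not change. The ED and GP events are needed to build the primary endpoint as the Abstract defines it, and consultations and emergency use are recorded for the economic evaluation. The Discussion says follow-up was still running when the article was written, so at that stage the endpoints could still be specified before analysis. The downside is two more secondary comparisons of limited precision.
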